[13]. Two further observational studies comparing standard to silver-impregnated EVDs have also shown a reduction in infection rates
[14,15]. The commentary accompanying the EVD study acknowledges the need for a RCT to study the relative benefits of silver-impregnated catheters.

Data from the UK shunt registry (to which most neurosurgical units contribute) show that 15% of shunt revisions are for infection
[16]. In the largest randomised controlled shunt trial worldwide, the infection rate was 8.4% for primary VPS
[17]. The commonest pathogens detected are *Staphylococcus* species, but in a proportion of patients with suspected infection the organism is never determined, especially if they have already received antimicrobial treatment or the organism is very slow growing, hampering microbiologically directed treatment selection. However newer molecular approaches are increasing the diagnostic rate for a range of central nervous system (CNS) infections. Whilst a systematic review
[9] suggests that antibiotic-impregnated shunts may be an effective way of reducing the incidence of shunt infections, there is some evidence that antibiotic-impregnated VPS that become infected may be more difficult to treat leading to prolonged hospital stays
[18]. Antibiotic-impregnated VPS prevent the sensitive organisms causing infection and may allow the rifampicin-resistant organisms to survive. Subsequently this may contribute to VPS failure secondary to infection. A second follow-up report of 500 antibiotic-impregnated primary and revision VPS insertions showed sensitive organisms may still cause infection but presentation was significantly delayed compared to standard historical controls
[19]. It is plausible to suggest that antibiotic-impregnated VPS may lead to a delay in presentation allowing increased time for biofilm development on the ventricular surface rather than just the VPS. This could result in more difficult to treat, serious infection through rifampicin resistance, and warrants further investigation.

There are no economic evaluations of VPS, however four retrospective cost studies from the USA

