### Proposed sample size

Approximately 30% of new VPS will fail within the first 6 months of insertion due to shunt complications, which will include infection but also malfunction and mechanical failure, typically secondary to catheter or valve obstruction and peritoneal complications. When a VPS has failed for reasons other than infection then this prevents infection being observed. Infection is the event of interest with all other reasons for shunt failure being competing risks. The trial will compare antibiotic-impregnated versus standard VPS, and silver-impregnated versus standard VPS. A Bonferroni adjustment has been made to allow for the multiple comparisons and a statistical significance level of 0.025 will be used accordingly. The sample size calculation is based on Pintilie
[24] assuming time to any type of event (of interest or competing risks) follows an exponential distribution. Using a 2-year accrual period with 6-month follow-up, once accrual has been completed and a competing risks event rate of 30% across trial arms with the event rate of interest (infection) being 8% in the standard arm and 4% in the treated arms (hazard ratio of 0.49), then with 5% loss to follow-up we would require 989 patients to provide 80% power. The power varies according to changes in the event rate with a fixed total sample size of approximately 1,143. Allowing for 5% loss to follow-up a sample size of 1,200 participants allows a hazard ratio of 0.49 to be detected over a range of baseline event rates (0.05 to 0.1) with good statistical power. The value of 8% is supported elsewhere

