### Statistical analysis

The primary analysis will be by intention-to-treat principle as far as is practically possible and a full statistical analysis plan will be developed prior to comparative analysis. Results will be presented throughout using 97.5% confidence intervals and a 2.5% level of statistical significance. Analysis of the primary outcome will be by cumulative incidence. The Fine and Gray
[25] regression method will be used to directly model the cumulative incidence function. In addition two semi-parametric models described in Scheike and Zhang
[26] will be used to consider time-varying effects. Time-to-event outcomes where competing risks is not an issue will be analysed using Kaplan–Meir curves, log-rank tests, and Cox proportional hazard models. Assumptions of proportional hazards will be investigated. Categorical outcomes will be analysed using Chi-squared test. An interim analysis will be conducted halfway through the trial after approximately 50% of the total events have been observed using Haybittle
[27].

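### The sample-size section claims good power for baseline infection rates of 0.05 to 0.1, but its own method gives about 67% at 0.05 and 76% at 0.06, below its 80% target

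*Protocol article*

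**What the plan says.** All of the following is in the Protocol article, Methods/design, Proposed sample size, unless noted.

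- Planning case: infection "being 8% in the standard arm and 4% in the treated arms (hazard ratio of 0.49"), with "a competing risks event rate of 30% across trial arms", exponential event times, two years of accrual and six further months of follow-up.
- Significance: after a Bonferroni adjustment for two comparisons with standard VPS, "a statistical significance level of 0.025 will be used accordingly". The Statistical analysis section adds: "Results will be presented throughout using 97.5% confidence intervals and a 2.5% level of statistical significance".
- Requirement: "then with 5% loss to follow-up we would require 989 patients to provide 80% power".
- Robustness: "The power varies according to changes in the event rate with a fixed total sample size of approximately 1,143". After allowing for 5% loss, the recruited total is 1,200, which "allows a hazard ratio of 0.49 to be detected over a range of baseline event rates (0.05 to 0.1) with good statistical power".

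The only numerical power target in the article is the 80% attached to 989 patients.

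**The concern.** For a fixed number of patients and a fixed hazard ratio, power depends on the number of infections observed, and that number falls almost in proportion to the baseline rate. Going from 989 to 1,200 adds about a fifth to the sample. Going from a baseline of 8% to 5% removes more than a third of the infections. The extra patients therefore cannot hold power near 80% at the lower end of the range.

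The sentence carries weight because it is the reason the article gives for 1,200 rather than 989. Its purpose is to reassure readers about a lower infection rate than planned, and that is where it does not hold. If the baseline rate were 0.05, each comparison would have about a one-in-three chance of missing the target effect, against the one in five that the plan set itself.

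**Working it through.** **Inputs.** From Proposed sample size: 6-month infection rates of 8% and 4%; competing events 30% in every arm; accrual a = 2 years; further follow-up f = 0.5 years; significance level 0.025 per comparison; power 80%; loss 5%; 1,143 evaluable patients. From Randomisation: 1:1:1 allocation, so each comparison uses two thirds of the total. Two inferences are needed. The test is taken as two-sided because a 97.5% interval is paired with a 2.5% level. The rates are taken as 6-month rates because the 30% failure figure is given at 6 months.

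**Formulas.** For an arm with 6-month infection rate p and competing rate 0.30:

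- total hazard L = −ln(1 − p − 0.30)/0.5; infection hazard l = L·p/(p + 0.30)
- probability of an observed infection P = (l/L)·[1 − (e^(−Lf) − e^(−L(a+f)))/(L·a)]
- infections needed per comparison = (2.2414 + 0.8416)²/(0.25·(ln HR)²)
- power = Φ(√(d/4)·|ln HR| − 2.2414), where d is the expected number of infections per comparison

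**Step 1: reproduce 989.**

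- Standard arm (8%): L = 0.956, l = 0.201, P = 0.1524.
- Treated arm (4%): L = 0.831, l = 0.0978, P = 0.0798.
- HR = 0.0978/0.201 = 0.486 (article: 0.49). Mean P = 0.1161.
- Infections needed = 72.9. Patients per comparison = 72.9/0.1161 = 628. Three arms: 628 × 1.5 = 942.
- With loss: 942 × 1.05 = 989, the stated figure. In the same way 1,143 × 1.05 = 1,200.

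**Step 2: the same method at 1,143 evaluable (762 per comparison), halving the baseline rate in the treated arm.**

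| Baseline rate | Infections per comparison | HR | Power |
|---|---|---|---|
| 0.05 | 56.9 | 0.491 | 67.0% |
| 0.06 | 67.6 | 0.489 | 75.7% |
| 0.07 | 78.1 | 0.488 | 82.5% |
| 0.08 | 88.4 | 0.486 | 87.6% |
| 0.09 | 98.6 | 0.484 | 91.3% |
| 0.10 | 108.5 | 0.482 | 94.1% |

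Worked line for 0.05: P = 0.0986 and 0.0508, mean 0.0747; d = 762 × 0.0747 = 56.9; √(56.9/4) × |ln 0.4913| = 2.681; Φ(2.681 − 2.241) = 0.670. Power reaches 80% at a baseline of about 0.066.

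**Step 3: size needed at 0.05.** Infections needed = 75.3. Divided by 0.0747 this is 1,008 per comparison, and × 1.5 = 1,512 evaluable. With loss, 1,512 × 1.05 = 1,588 recruited. The like-for-like comparisons are 1,512 with 1,143 and 1,588 with 1,200.

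**Step 4: sensitivity.**

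- HR held at exactly 0.49: 67.2% at 0.05 and 75.4% at 0.06.
- All 1,200 evaluable, no loss: about 69% to 70% at 0.05 and 78% at 0.06.
- 30% read as total failures including infection: 67% to 70% at 0.05 and 76% to 79% at 0.06.
- One-sided 0.025: 76% at 0.05; this choice does not reproduce 989.
- Simulated cause-specific log-rank test, 381 per arm: 64% to 66% at 0.05 and 72% to 74% at 0.06.
- Simulated Fine and Gray test, the planned primary analysis: about 62% at 0.05, 70% at 0.06, 77% at 0.07, 82% to 83% at 0.08 and 90% at 0.10.

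**The case against.** The strongest reply is that the sentence promises no number. The article says good power, not 80%, and it warns that power varies with the event rate. The 80% belongs to 989 patients at an 8% baseline. No printed figure is wrong, so calling the sentence simply false would go too far. This stands. What remains is that a section whose only benchmark is 80% describes 67% as good.

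It is also true that the claim holds for about two thirds of the range (0.066 to 0.10) and at the planning value. An article may leave a power table to the full protocol. But the point here is a positive statement that the article's own method does not support, not a missing table.

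Stronger readings are tempting, and the documents do not support them:

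- *That a rate near 5% is to be expected.* A reader might multiply the registry figure, "15% of shunt revisions are for infection", by 30% failure in six months and get 4.5%. The registry figure is not restricted to first shunts or to six months, so the denominators differ. The article's direct evidence points to 8%: 8.4% for primary VPS in the largest randomised shunt trial, and ten years of surveillance over more than 1,500 insertions at around that level.
- *That power is much lower still because infections occur early.* That drops the exponential assumption on which the calculation rests, so it cannot show that the plan's method contradicts its own sentence.
- *That funders or the monitoring committee were misled.* The article does not show what those bodies were given.

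**Conclusion.** The point holds as a correction to one sentence. By the method that reproduces 989, power at 1,143 evaluable patients is below the plan's 80% target for baseline infection rates under about 0.066, and is about 67% at the lower limit the article names. From about 0.07 upward the claim is sound by the planning formula. At 8% power is about 88%, so neither the planning case nor 1,200 as a target for that case is undermined.

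The conclusion rests on a two-sided test, on rates read at six months, on exponential times, and on taking 80% as the yardstick for good power. Each reading of the inputs tried that reproduces 989 leaves power at 0.05 between about 67% and 70%.

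**What to change.** Replace the sentence with the power at each baseline rate: 67%, 76%, 82%, 88%, 91% and 94% at 0.05, 0.06, 0.07, 0.08, 0.09 and 0.10. A shorter alternative is to claim at least 80% power, by the planning formula, only for about 0.07 to 0.10, and to state that power at 0.05 is about 67% by that formula and about 62% by simulation of the Fine and Gray test.

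This costs one sentence or a small table and a less favourable stated figure. It needs no change to the sample size, the effect size or the analysis.

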### Statistical analysis

The primary analysis will be by intention-to-treat principle as far as is practically possible and a full statistical analysis plan will be developed prior to comparative analysis. Results will be presented throughout using 97.5% confidence intervals and a 2.5% level of statistical significance. Analysis of the primary outcome will be by cumulative incidence. The Fine and Gray
[25] regression method will be used to directly model the cumulative incidence function. In addition two semi-parametric models described in Scheike and Zhang
[26] will be used to consider time-varying effects. Time-to-event outcomes where competing risks is not an issue will be analysed using Kaplan–Meir curves, log-rank tests, and Cox proportional hazard models. Assumptions of proportional hazards will be investigated. Categorical outcomes will be analysed using Chi-squared test. An interim analysis will be conducted halfway through the trial after approximately 50% of the total events have been observed using Haybittle
[27].

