### Secondary objectives

• To determine the proportion of first VPS infections occurring >6 months after insertion of *de novo* VPS.

• To determine whether antibiotic or silver-impregnated VPS reduce shunt failure of any cause compared to standard VPS following insertion of *de novo* VPS.

• To assess whether the reason for shunt failure is different across the three different types of VPS.

• To determine which organisms and their resistance/sensitivities subsequently infect these three alternative VPS.

• To determine whether antibiotic or silver-impregnated VPS reduce infection following the first (non-infected) clean VPS revision for mechanical failure compared to standard VPS.

• To assess the impact of VPS infection on the patient in terms of quality of life.

• To assess the cost-effectiveness of antibiotic-impregnated and silver-impregnated VPS compared to standard VPS.

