### Secondary outcomes

• Time to shunt failure of any cause.

• Reason for shunt failure (infection, mechanical failure, patient failure, or other).

• Types of bacterial shunt infection (organism type and antibiotic resistance).

• Time to shunt infection following first clean revision.

• Quality of life.

• Incremental cost per shunt failure averted.

• Incremental cost per quality-adjusted life-year (QALY) gained.

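### A chi-squared test on reason for failure or organism type, if run only among failed or infected shunts, can show a difference when the risk of mechanical failure or resistant infection is unchanged

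*Protocol article*

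**What the plan says.** The Statistical analysis section of the protocol article gives one method for this kind of endpoint: "Categorical outcomes will be analysed using Chi-squared test". It names cumulative incidence and Fine and Gray regression for the primary outcome only.

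Two items under Secondary outcomes are categorical: "Reason for shunt failure (infection, mechanical failure, patient failure, or other" and "Types of bacterial shunt infection (organism type and antibiotic resistance". The matching objectives differ in kind. One is comparative: "To assess whether the reason for shunt failure is different across the three different types of VPS". The other is worded descriptively: "To determine which organisms and their resistance/sensitivities subsequently infect these three alternative VPS".

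The article recognises both mechanisms that matter here. The sample size section states "Infection is the event of interest with all other reasons for shunt failure being competing risks". The Background states "Antibiotic-impregnated VPS prevent the sensitive organisms causing infection and may allow the rifampicin-resistant organisms to survive", and adds that any benefit has to be weighed against selecting resistant organisms.

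The denominator for the chi-squared test is not given. A full statistical analysis plan is promised before comparative analysis.

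**The concern.** A shunt that has not failed has no reason for failure, and a shunt that is not infected has no organism. The natural table therefore has failed shunts, or infected shunts, as its denominator. Randomisation does not protect that comparison, because the catheter is intended to change who enters the table.

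Two consequences follow.

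- Any reduction in infection raises the share of failures due to other causes, even if no catheter fails mechanically more often.
- If the infections prevented are the sensitive ones, the resistant share of the remaining infections rises, even if no patient has a higher risk of resistant infection.

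The second is the question the Background wants answered. A test among infected shunts cannot separate selection of resistant organisms from prevention of sensitive ones. A real benefit could then be entered on the harm side when catheters are compared.

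**Working it through.** **Inputs from the article (Proposed sample size, Randomisation).** Infection "being 8% in the standard arm and 4% in the treated arms (hazard ratio of 0.49"; competing events 30% in all arms; accrual 2 years plus 6 months of follow-up, so 6 to 30 months per patient; 1,200 patients 1:1:1, so 400 per arm; significance level 0.025, taken as two-sided. All competing failures are treated below as one non-infection group.

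**Assumption not in the article.** The resistant share of standard-arm infections: 10%, 20% or 30%.

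**1. Check that the rates are read as the plan reads them.** Take 8% or 4% and 30% as 6-month cumulative incidences with exponential times.

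- Standard arm: total hazard −ln(1 − 0.38)/0.5 = 0.956 per year, split as infection 0.956 × 8/38 = 0.201 and competing 0.956 × 30/38 = 0.755.
- The cause-specific hazard ratio for 8% v 4% is 0.486.
- Events needed: 4 × (2.241 + 0.842)² / (ln 0.486)² = 72.9.
- Probability of infection over the trial: 0.152 and 0.080, mean 0.116. 72.9/0.116 ≈ 628 patients per two-arm comparison; × 1.5 = 942; / 0.95 = 992.

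The plan states 989, so the rates are read correctly and the sample size is not in question.

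**2. Share of non-infection failures, by arithmetic.** Standard 30/38 = 79%; treated 30/34 = 88%. With 400 per arm this is 32 infections and 120 other failures against 16 and 120. Pearson chi-squared = 288 × (32 × 120 − 120 × 16)² / (152 × 136 × 48 × 240) = 4.46, p = 0.035. The 2.5% critical value is 5.02, so the expected table falls just short and rejection is close to a coin toss.

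**3. Rejection rates, one impregnated arm v standard.** Competing hazard 0.755 in both arms; infection hazard 0.201 v 0.201 × 0.49 = 0.099; chi-squared at 0.025.

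| Non-infection failure | 6 months | 6 to 30 months |
|---|---|---|
| Among failed shunts | about 48% | about 80% |
| Per randomised patient | about 3% | about 11% |

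With the 6-month cumulative incidence (not the hazard) of other failures held equal at 30%, the first row at 6 months is 45% and the second 2.5%. If the 30% is read as including infection (22% competing), the share moves from 22/30 = 73% to 22/26 = 85% and the among-failures test rejects in about 43%.

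**4. Resistant infection.** The resistant hazard is the same in both arms; the whole reduction comes from sensitive infections.

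| Assumed resistant share, standard arm | 10% | 20% | 30% |
|---|---|---|---|
| Resistant share, treated arm | 20% | 41% | 61% |
| Infected only, 6 months (about 32 v 16 infections) | 12% | 25% | 44% |
| Infected only, 6 to 30 months (about 61 v 32) | 21% | 46% | 75% |
| Per randomised patient, either horizon | 2–3% | 2–3% | 2–3% |

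At 6 months the smallest expected cell is 16 × 6.4/48 = 2.1 for a 10% share and 16 × 12.8/48 = 4.3 for 20%. This is before any split by organism or across three arms.

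**5. Is the all-randomised denominator enough?** For resistant infection, yes. For mechanical failure, not quite. With equal competing hazards, the cumulative incidence of non-infection failure over 6 to 30 months is 57% in the standard arm and 61% in the treated arm, because fewer infections leave more shunts at risk. That produces the 11% in step 3. The cause-specific hazard ratio in the same setting is 1.

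**The case against.** The strongest reply is that the article never restricts the test to failed or infected shunts. A chi-squared test of failure category, with no failure as one category, over all randomised patients also fits the sentence, and the denominator is a detail that an analysis plan can settle. This stands in part: a reader might infer that the plan fixes a subset test, and the text does not support that. It does not dispose of the point. The stated method is chi-squared under either reading, and over all randomised patients it still takes no account of 6 to 30 months of differing follow-up or of the competing risks that the article recognises.

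Second, a changed mix of reasons is a true answer to the comparative objective as worded, the organism objective is descriptive, and nothing commits the trial to a causal reading. That also stands. The error would lie in reading a changed mix as harm.

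Third, a reader might infer that an effective catheter will inevitably look harmful. The shift in shares is expected, but significance is not assured: about 48% at 6 months for failure mix, and far less for resistance if resistant organisms are rare.

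Fourth, the resistance figures rest on a share that the article does not give and on an extreme case in which every prevented infection is a sensitive one. The Background offers that mechanism for the antibiotic catheter only. The 6 to 30 month figures also extend constant hazards to a point where about 72% of standard-arm shunts have failed (0.152 + 0.571). The 6-month figures are the safer guide.

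**Conclusion.** The concern holds conditionally. If the chi-squared test is run among failed or infected shunts, which is how these outcomes are naturally observed, it can reject with no change in the hazard of mechanical failure or resistant infection.

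The failure-mix result needs only the plan's own rates and unchanged competing hazards, and it follows from any reduction in infection, whatever the organism. The resistance result needs the two added assumptions above and should be quoted with its range.

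These are secondary outcomes. The primary analysis and the sample size are unaffected. The change is nonetheless worth making, because resistance is the main harm that the article sets against benefit.

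**What to change.** In the analysis plan, replace the chi-squared test for these two outcomes as follows.

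- **Denominator:** all randomised patients.
- **Events:** each failure cause (infection, mechanical, patient, other), and each infection type (resistant, sensitive, culture-negative). The last category is needed because the Background notes that the organism is sometimes never identified.
- **Estimates:** cumulative incidence together with cause-specific hazard ratios, each impregnated arm against standard, with 97.5% confidence intervals. Cumulative incidence or Fine and Gray alone is not enough for mechanical failure, for the reason in step 5 of the working.
- **Mix among failed or infected shunts:** descriptive only, with exact tests if any are wanted, and a sentence saying that a changed mix is not by itself evidence of harm.

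The cost is a revision of analysis-plan wording and a few extra models on data already collected. Cumulative incidence, Fine and Gray and Cox models are already named in the article. Resistant infections will be few, so those intervals will be wide, and the report should say so.
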